#### Secondary effectiveness analyses

##### Quantitative outcomes

Secondary quantitative outcomes (weight, blood pressure, GPAQ total physical activity score, weight monitoring frequency, blood glucose monitoring frequency, diabetes medication adherence frequency, DSMQ sum score, global PSQI score, percent overall work impairment and percent activity impairment due to diabetes and related health problems using a modified WPAI:SHP, health utility index using 5-level EQ-5D) will be analyzed using a similar strategy as applied to the primary outcome. A linear regression model will be used to model the secondary quantitative outcome as the dependent variable and an intercept, the outcome at baseline (quantitative variable), indicator variables for participants who received DMP alone and participants who received DMP plus M-POWER, and indicator variables for stratification factors (gender, diabetes center, and dichotomized HbA_1c_ level at baseline) as independent variables. Additional analyses will also be performed to evaluate the intervention effects that account for insulin progression/medication changes and other potential effect modifiers, mediators, covariates, and program engagement metrics.

##### Binary outcomes

Secondary binary outcomes (e.g., proportion of participants who had insulin treatment initiated by their diabetes care physician) will be analyzed using a generalized linear model with a log link function and binomial distribution (log-binomial regression model). The model will include the following as independent variables: an intercept, indicator variables for participants who received DMP alone and participants who received DMP plus M-POWER, and indicator variables for stratification factors (gender, diabetes center, and dichotomized HbA_1c_ level at baseline).

#### Secondary cost-effectiveness analyses

The net cost and cost-effectiveness analysis will be performed from a third-party payer’s perspective using an activity-based costing approach which the principal investigator has performed in many prior studies [36–38]. Using this approach, the costs of program delivery will be determined by capturing data on all non-sunk labor costs, materials and supplies, contracted services (including costs for GlycoLeap), and M-POWER Rewards payouts. Billing data from inpatient, outpatient, pharmacy, and emergency departments will be collected. We will compute the net costs of each arm and the incremental cost per unit reduction in HbA_1c_ at Month 12 (primary endpoint) as compared to the next most costly intervention. We will also compute the incremental cost per QALY gained based on published studies/models that quantify the relationship between reductions in HbA_1c_ at Month 12 and QALYs gained. Results will be compared to established benchmarks for cost-effectiveness and those of other interventions aimed at reducing HbA_1c_ levels. As a secondary analysis, we will also quantify incremental costs per QALY gained based on the 5-level EQ-5D health utility index captured at Month 12 through questionnaires and assumptions about the duration of any benefits attained during the study. One-way and *n*-way sensitivity analyses and cost-effectiveness acceptability curves that graphically present the probability that each intervention arm is incrementally cost-effective (and potentially cost-saving) for a range of willingness-to-pay metrics that a decision maker may consider will also be presented.

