#### Secondary objectives

The secondary objectives are to determine net costs and incremental cost-effectiveness ratios (ICERs) of each intervention arm. ICERs will be calculated based on costs per improvement in HbA_1c_ at Month 12 and converted to cost per quality-adjusted life year (QALY) gained. Using established benchmarks for cost-effectiveness [21, 22], we hypothesize that DMP alone will be cost-effective compared to usual care and, despite higher implementation cost, DMP plus M-POWER will be incrementally cost-effective relative to DMP alone.

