
#### Participant retention

Participants will receive SGD30 at each assessment for successfully completing assessments within their respective window periods. Participants in the usual care arm and the DMP incentive arm will receive SGD150 and SGD70, respectively, as forms of “fairness” payouts for not receiving the DMP and/or incentives entitled to other arms. Table 3 lists the participant payouts by arm.

**Table 3 Tab3:** Participant payouts

Type of payout	Condition	Payouts		
		Arm 1 (Usual care)	Arm 2 (DMP)	Arm 3 (DMP plus M-POWER)
Attending training session	Attend the training session	SGD10	SGD10	SGD10
Completing assessments	Complete assessments at Months 6, 12, 18, and 24 within their respective window periods	SGD30 per assessment	SGD30 per assessment	SGD30 per assessment
Study device data upload	Each device (pedometer, glucometer, and pill tracker) needs to contain at least one entry within the first 7 calendar days from the first Monday (inclusive) of the month to receive payouts for that device for that month The data must be uploaded successfully	NA	SGD2 per device per month^a^	SGD2 per device per month^a^
M-POWER Rewards	As per M-POWER Rewards scheme (Tables 1 and 2)	NA	NA	Max 1000 M-Points (SGD1000) over 104 weeks
Fairness payout	Complete both Month 12 and Month 24 assessments within their respective window periods Awarded upon completion of the Month 24 assessment	SGD150 for entire study^b^	SGD70 for entire study^c^	NA

^a^SGD6 per month for three devices (pedometer, glucometer, and pill tracker) in total

^b^For not receiving DMP, incentives for study device data upload, and M-POWER Rewards

^c^For not receiving M-POWER Rewards

Participant burden will be minimized by limiting participant in-person visits to five sessions (one baseline and four follow-up assessments), although additional visits may be necessary to disburse cash payouts or provide replacement devices. Malfunctioned or misplaced devices will be replaced at a subsidized rate (depending on budget) to enable continued participation of participants in the intervention arms.

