#### Data for sensitivity analysis and cost-effectiveness analysis

Medical data such as HbA_1c_ test results taken during usual care at the clinics and diabetes medications prescribed and purchased, including insulin initiation dates, will be obtained from the medical records and pharmacy bills of all participants. HbA_1c_ test results from these medical records will be used in sensitivity analyses. Billing data from inpatient, outpatient, pharmacy, and emergency departments will be collected to estimate net costs and cost offsets for the cost-effectiveness analysis. The costs of program delivery will be determined by capturing data on all relevant (non-sunk) labor costs, materials and supplies, contracted services (including costs for GlycoLeap), and M-POWER Rewards payouts.

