#### Study devices and apps

To encourage participants in the incentive arms to engage with the study components, weekly inactivity notifications that list the components that they have not been engaging with will be emailed to participants. Participants who are not engaging with the study components will be contacted by the study team, who will offer their assistance and ensure that participants are not experiencing problems with the devices or apps. Study team members will also note those who indicate that they do not wish to perform any activity(s) and will not contact these participants for the purpose of troubleshooting. At each follow-up assessment, study team members will also verify that participants are using the devices as instructed and respond to any queries that participants might have on usage of the devices or apps. Besides the aforementioned measures to reduce data loss, participants in both intervention arms will be incentivized to upload their data: participants will be given SGD2 per device per month for syncing their pedometers, glucometers, and pill trackers with their anonymous study accounts see (Table 3).

As participants in the DMP plus M-POWER arm may be tempted to cheat in order to earn more M-Points, they will sign a participant oath at the end of the training session and each time they collect their M-Points redemption payouts. This might help to improve data validity, as such oaths could reduce the likelihood of cheating [24]. The study team will also manage and back up data from the devices and apps and regularly check the data for inconsistencies that may suggest cheating.

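### The program cost list leaves out the device-upload payments made only in the two intervention arms, so the DMP versus usual care ICER should be shown with and without them

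*Protocol article*

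**What the plan says.** The cost components appear twice in the protocol article, with the same content.

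- **Data for sensitivity analysis and cost-effectiveness analysis:** "The costs of program delivery will be determined by capturing data on all relevant (non-sunk) labor costs", followed by materials, contracted services and the M-POWER Rewards payouts.
- **Secondary cost-effectiveness analyses:** the list again, ending in "materials and supplies, contracted services (including costs for GlycoLeap), and M-POWER Rewards payouts". The viewpoint is fixed there too: "The net cost and cost-effectiveness analysis will be performed from a third-party payer’s perspective using an activity-based costing approach". The ratio is the "incremental cost per unit reduction in HbA_1c_ at Month 12 (primary endpoint) as compared to the next most costly intervention".

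The device-upload payments are described elsewhere.

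- **Study devices and apps** (under Data management and monitoring): in both intervention arms, "participants will be given SGD2 per device per month for syncing their pedometers, glucometers, and pill trackers".
- **Participant retention, Table 3:** a device earns the payment for a month only if it holds at least one entry in a set seven-day window and the data are uploaded. The usual care column reads NA. Footnote a gives the total: "SGD6 per month for three devices (pedometer, glucometer, and pill tracker) in total".
- **Table 3, footnote b:** usual care receives its SGD150 fairness payout "For not receiving DMP, incentives for study device data upload, and M-POWER Rewards". Footnote c gives the SGD70 payout in Arm 2 only for the lack of M-POWER Rewards.

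Under Secondary objectives the hypothesis is stated: "we hypothesize that DMP alone will be cost-effective compared to usual care".

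**The concern.** An ICER is informative only if its cost and its effect describe the same program. Participants in Arm 2 produce their Month 12 HbA1c while being paid for device entries and uploads. The listed cost of Arm 2 contains no such payment. Usual care receives none, so the omission does not cancel in the DMP versus usual care comparison, which is the one the hypothesis about DMP alone rests on. The Background says that third-party payers may fund the program if it proves cost-effective. Such a payer would need to know whether the quoted ratio includes these payments.

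**Working it through.** **Inputs**

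- Payment: SGD2 per device per month, three devices, Arms 2 and 3 only (Table 3).
- ICER time point: Month 12 (Secondary outcomes; Secondary cost-effectiveness analyses).
- Planned DMP versus usual care difference: 0.5 percentage points of HbA1c (Sample size).
- Assumption: full uptake, with all three devices qualifying in each of 12 months. This gives an upper bound.

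**Step 1, the protocol's own figure.** 3 devices × SGD2 = SGD6 per month, which agrees with Table 3, footnote a.

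**Step 2, maximum by Month 12.** SGD6 × 12 = SGD72 per participant in Arm 2, and SGD0 in Arm 1.

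**Step 3, effect on the ICER.** Addition to the ICER = omitted incremental cost / HbA1c difference.

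| HbA1c difference (points) | Addition, SGD per point |
|---|---|
| 0.5 (planned) | 72 / 0.5 = 144 |
| 1.0 (assumed) | 72 / 1.0 = 72 |
| 0.3 (assumed) | 72 / 0.3 = 240 |

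The addition scales with uptake. Half uptake would halve every entry.

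**Step 4, DMP plus M-POWER versus DMP.** The omitted difference is SGD72 × (uptake in Arm 3 − uptake in Arm 2). It is zero at equal uptake, so only a difference in upload rates remains.

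**Step 5, relative size.** The documents give no other program cost for DMP. With an assumed incremental cost, before the payments, of SGD200 to SGD2000 per participant, adding them raises it by 72/200 = 36% down to 72/2000 = 3.6%. The range is wide because the base is unknown. The ICER per QALY that is converted from the HbA1c ICER rises by the same percentage. Its change in SGD cannot be computed, since the conversion is not given.

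**Step 6, what the uploads serve.** HbA1c, weight and blood pressure are measured at study visits (Health outcomes). The self-care outcomes come from questionnaires (Secondary outcomes; Survey data), and insulin initiation and costs from medical and billing records. None of these needs a device upload. The uploads feed the M-POWER app's progress displays, peer comparisons and streaks, and glucometer data synced to the Glyco app are available to the coaches (Arm 2; Study devices and apps under Data collection). They also supply the program engagement metrics for additional analyses. So the uploads help to run the intervention as well as to supply research data.

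**The case against.** The strongest reply is that the payments are a research cost, which a payer's costing properly leaves out. The text gives this real support. Table 3 sits under Participant retention, beside the payments for attending training and completing assessments. The section on study devices and apps presents the upload payments as one more safeguard against data loss. The Discussion groups syncing incentives with assessment incentives and separates both from rewards for care processes and outcomes. This stands as a tenable classification, but it does not settle the matter. The effectiveness outcomes do not depend on uploads, the payment requires a device entry and not merely a sync, and footnote b treats the payments as a benefit that usual care lacks.

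A second reply is that a condensed article may leave item-level costing to a fuller plan, and that the planned one-way and n-way sensitivity analyses could cover this item. That is fair as to severity. Still, the article does give a component list, twice, and this payment is not in it.

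A third reply points to the fairness payouts, which favor Arm 1 by SGD150 − SGD70 = SGD80. If every Table 3 payout were counted over 24 months, the maxima would be 10 + 4 × 30 + 150 = SGD280 in Arm 1 and 10 + 4 × 30 + 24 × 6 + 70 = SGD344 in Arm 2, a gap of SGD64. But the fairness payouts are awarded only on completing Month 24, so they do not offset the Month 12 figure. They also compensate for what an arm did not receive and deliver no part of a program.

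Some stronger readings are tempting, and the documents do not support them:

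- A reader might infer that M-POWER Rewards is the only cost counted. Labor, materials and contracted services are counted too; it is only the sole participant payment.
- A reader might infer that the protocol presents Arm 2 as free of any payment. It describes DMP with or without M-POWER Rewards and discloses the upload payments openly.
- A reader might infer that the measured effect would be lost without the payments. Nothing in the documents shows how much of any HbA1c change would come from SGD2 for a single qualifying entry per device per month.
- A reader might divide the 24-month payments by the Month 12 difference. That mixes two time horizons, and the ICER is defined at Month 12.

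**Conclusion.** The point holds in conditional form. The program cost list omits a participant payment made only in Arms 2 and 3, and the article does not say whether it is a program or a research cost. If it belongs to the delivered DMP, the Month 12 ICER against usual care is too favorable by at most SGD72 per participant. That is SGD144 per percentage point of HbA1c, assuming full uptake and the planned 0.5-point difference. If it is purely a research cost, there is no bias. It would therefore go too far to say outright that the ICER is understated. The comparison of the two intervention arms is largely unaffected. Whether the amount matters relative to the whole DMP cost cannot be judged from the documents. This is a cheap improvement to the costing and does not show that the economic result is wrong.

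**What to change.** In the cost-effectiveness plan:

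1. Report the DMP versus usual care ICER, per HbA1c point and per QALY, both with and without the upload payments actually made.
2. State which version treats the payments as a program cost and which as a research cost.
3. Describe Arm 2 in the conclusions as DMP with data-upload payments.

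The amounts should be available from the trial's payout records, and the second version fits within the sensitivity analyses already planned. The cost is one extra analysis, and one version of the ICER will be slightly less favorable to DMP.

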**Discussion:**

The TRIPOD study will present insights about the long-term cost-effectiveness and financial viability of the interventions and the potential for integrating within usual care.

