In a previous feasibility study, we evaluated a proprietary lifestyle management program, GlycoLeap (designed and produced by KKT Technology Pte. Ltd., Holmusk, Singapore), which was originally developed for adults with T2DM in Singapore [14]. The 24-week GlycoLeap program consisted of a comprehensive T2DM educational curriculum delivered online and the Glyco smartphone app, through which users logged and monitored their blood glucose levels, weight, meals, and physical activity and received personal health coaching by accredited dietitians. Although we observed statistically significant improvements in HbA_1c_ (− 1.3 percentage points, *P* < 0.001) and weight reduction (2.3% reduction from baseline weight, *P* < 0.001), the proportion of participants meeting recommended weekly self-care process targets declined throughout the 24-week period for all evaluated components, potentially attenuating the longer term benefits of sustained lifestyle management [14]. To address this concern, we have developed a rewards program based on behavioral economic theory to complement GlycoLeap. The rewards program leverages present bias, loss aversion, and habit formation and thus offers the potential for lasting benefits.

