#### Secondary outcomes

The secondary outcomes are:
Mean change in HbA_1c_ level at Months 6, 18, and 24 from baselineMean change in weight at Months 6, 12, 18, and 24 from baselineMean change in systolic and diastolic blood pressure at Months 6, 12, 18, and 24 from baselineProportion of participants who had insulin treatment initiated by their diabetes care physician by Months 6, 12, 18, and 24Mean change in self-reported physical activity at Months 6, 12, 18, and 24 from baseline as assessed using the Global Physical Activity Questionnaire (GPAQ) [26]Mean change in self-reported weight monitoring at Months 6, 12, 18, and 24 from baseline as assessed by frequency of self-weighingMean change in self-reported blood glucose monitoring at Months 6, 12, 18, and 24 from baseline as assessed by frequency of self-testingMean change in self-reported medication adherence at Months 6, 12, 18, and 24 from baseline as assessed by frequency of taking diabetes medications as prescribedMean change in diabetes self-management at Months 6, 12, 18, and 24 from baseline as assessed using the Diabetes Self-Management Questionnaire (DSMQ) [27]Mean change in sleep quality at Months 6, 12, 18, and 24 from baseline as assessed using the Pittsburgh Sleep Quality Index (PSQI) [28]Mean change in work productivity and daily activity impairment at Months 6, 12, 18, and 24 from baseline as assessed using a modified Work Productivity and Activity Impairment: Specific Health Problem instrument (WPAI:SHP) [29]Mean change in health utility index at Months 6, 12, 18, and 24 from baseline as assessed using the 5-level EQ-5D instrument [30]ICERs based on HbA_1c_ level, determined by calculating the incremental cost per percentage point unit reduction in HbA_1c_ level at Month 12 (primary endpoint)ICERs based on QALYs, determined by converting ICER based on HbA_1c_ level into incremental cost per QALY gained.

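### Both QALY calculations take only Month 12 effects, although EQ-5D-5L and HbA1c are measured to Month 24, so persistence over the second year need not be assumed

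*Protocol article*

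**What the plan says.** The section Secondary cost-effectiveness analyses names three effect inputs, all at Month 12:

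- The main ICER is "the incremental cost per unit reduction in HbA_1c_ at Month 12 (primary endpoint) as compared to the next most costly intervention".
- The first QALY result comes from "published studies/models that quantify the relationship between reductions in HbA_1c_ at Month 12 and QALYs gained".
- A further QALY result, labelled secondary within that section, is "based on the 5-level EQ-5D health utility index captured at Month 12 through questionnaires and assumptions about the duration of any benefits". The sentence goes on to specify benefits gained within the study.

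The trial measures more than this. Under Secondary outcomes the utility endpoint is "Mean change in health utility index at Months 6, 12, 18, and 24 from baseline as assessed using the 5-level EQ-5D instrument", and HbA1c change is listed there at Months 6, 18 and 24. Under Data collection, questionnaires and blood tests are scheduled at baseline and at all four follow-up visits. The intervention lasts 104 weeks (Study design), and rewards can be earned throughout (Tables 1 and 2).

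On costs, the article says "Billing data from inpatient, outpatient, pharmacy, and emergency departments will be collected to estimate net costs and cost offsets for the cost-effectiveness analysis". It gives no period for the billing data and none for the costs entering the ICERs. The abstract promises "insights about the long-term cost-effectiveness and financial viability of the interventions".

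**The concern.** A QALY gain is a utility difference accumulated over time. Taking one time point and supplying the duration by assumption is reasonable when follow-up stops there. Here it continues for another year with the same instrument, so part of the duration is observable.

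The second year is also where the effect is least certain. The education and coaching programme ends after 24 weeks, and in the sponsor's feasibility study "the proportion of participants meeting recommended weekly self-care process targets declined throughout the 24-week period for all evaluated components". The rewards were designed to counter that decline and run to week 104, so whether they do so is a central question for a payer. An economic result built from Month 12 alone cannot answer it, although the abstract presents long-term cost-effectiveness as a product of the trial.

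**Working it through.** **Figure in the plan.** The cost-effectiveness section states no effect size or QALY to reproduce. The cap of 1000 M-Points (SGD1000) can be checked from Tables 1 and 2:

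- To week 104: 8 + 24 + 104 + 312 + 208 + 104 + 4 × 60 = 1000. The cap reproduces.
- To week 52, assuming that all quizzes are passed by then and that the starting bonus and the Month 6 and Month 12 goal bonuses are counted: 8 + 24 + 52 + 156 + 104 + 52 + 2 × 60 = 516.
- Ratio: 1000 / 516 = 1.94. The maximum falling after week 52 is 1000 − 516 = SGD484 per Arm 3 participant.

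**QALY illustration.** The article gives no expected utility gain, so let u be the between-arm utility difference at Month 12. Assume a difference of 0 at baseline and 0.5u at Month 6. With visits half a year apart, the trapezoidal area is

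QALY = 0.5 × [(d0 + d6)/2 + (d6 + d12)/2 + (d12 + d18)/2 + (d18 + d24)/2].

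The first year gives 0.5 × (0.25u + 0.75u) = 0.50u in every row below. The last column divides the held value, 1.50u, by the measured area.

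| Months 12–24 (assumed) | d18, d24 | Second-year area | 24-month QALY | Held / measured |
|---|---|---|---|---|
| Month 12 gain held | u, u | 1.00u | 1.50u | 1.00 |
| Falls linearly to half | 0.75u, 0.5u | 0.75u | 1.25u | 1.20 |
| Falls linearly to zero | 0.5u, 0 | 0.50u | 1.00u | 1.50 |
| Lost by Month 18 | 0, 0 | 0.25u | 0.75u | 2.00 |
| Grows by half | 1.25u, 1.5u | 1.25u | 1.75u | 0.86 |

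The ratios do not depend on u. If u were 0.02, the held value would be 0.030 QALY, and the measured values, in table order from the second row, would be 0.025, 0.020, 0.015 and 0.035. At a fixed incremental cost, the ICER moves by the inverse of the ratio.

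**Month 6.** This visit matters too. If the difference were 1.5u at Month 6, u at Month 12, 0.5u at Month 18 and 0 at Month 24, the area would be 0.375u + 0.625u + 0.375u + 0.125u = 1.50u. That equals the held value from the table, because an early gain missed and a late loss missed happen to cancel. A single Month 12 value cannot tell these courses apart.

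**The case against.** Several points on the other side stand.

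- **Month 12 is a defensible base case.** It is the powered primary endpoint. The cost per unit of HbA1c at Month 12 needs no persistence assumption at all.
- **The EQ-5D calculation is a secondary analysis within a secondary section.** A reader might infer that the whole economic case rests on one EQ-5D value. It does not. The HbA1c-to-QALY route depends on persistence only through whatever its published models assume.
- **The duration assumption may be meant for the period after the study.** A reader might infer that the plan carries the Month 12 value through to Month 24. The article does not say so, and extrapolation beyond Month 24 does need assumptions.
- **Baseline utility is not ignored.** The quantitative-outcomes model already adjusts EQ-5D for its baseline value.
- **Evidence of waning is indirect.** The feasibility study saw fewer participants meeting process targets, in a programme without rewards, while HbA1c improved by 1.3 percentage points. It does not show loss of HbA1c or utility benefit in year two.
- **No cost mismatch is stated.** A reader might infer that 24-month costs will be divided by a Month 12 effect, or that billing is known to run to Month 24. The article fixes neither. Insulin initiation up to Month 24, dated from records and pharmacy bills, makes the longer period plausible for those sources only.

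These points narrow the concern but do not remove it. Even if the assumed duration begins after the study, Month 12 is the only utility named as input. The planned one-way and multi-way sensitivity analyses are not said to use later measurements. The Month 18 and 24 effectiveness tests will show whether benefit persists, but the article does not feed them into the cost-effectiveness result.

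**Conclusion.** The concern holds for the two QALY calculations: both are fixed on Month 12 inputs in a trial that measures the same quantities to Month 24. It does not touch the primary analysis or make the Month 12 HbA1c ICER wrong.

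The direction of error is unknown. Under the assumed courses above, holding the Month 12 gain gives between 0.86 and 2.0 times the measured 24-month QALYs. A reader might infer that the plan overstates QALYs by a definite percentage. The documents do not support that, since they give neither a utility gain nor a course over time, and the carry-forward used for comparison is itself an assumption. The reward totals of SGD516 and SGD1000 are maxima. They show why costs and effects need a common period, not that the plan mismatches them.

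**What to change.** 1. Keep the Month 12 HbA1c ICER and state that it uses costs to Month 12.
2. Compute the EQ-5D QALYs as the area under the curve over 0–24 months from all five visits, adjusted for baseline utility, and set them against costs over the same 24 months.
3. Confirm that billing data will cover 24 months.
4. Use the Month 18 and 24 HbA1c values in a sensitivity analysis of the HbA1c-to-QALY conversion.
5. Restrict assumed duration of benefit to the period beyond Month 24, and vary it in the sensitivity analyses already planned.

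The outcome measurements are already scheduled, so no visit is added. The cost is some extra analysis and more missing questionnaires at the late visits, for which a missing-data method such as imputation should be specified. If billing was to stop before Month 24, extending it is an added cost.
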